#### Secondary outcomes

Secondary outcomes will only be evaluated in the RCT part of the study and will be collected from birth until discharge home. Secondary outcomes include the following:
Sepsis-related severity of illness using the neonatal Sequential Organ Failure Assessment (nSOFA) score in infants treated with antibiotics > 3 days [16]. Severe illness is defined as a nSOFA score of ≥ 4 within the first 3 days of antibiotic treatment. The nSOFA score will be calculated 3 times a day within the first 3 days of antibiotic treatment. A cut-off value of 4 will be used to differentiate between severe illness and non-severe illness.Incidence of meningitis and sepsis-related mortality [16, 17]Total number of antibiotic days when started < 72 h after birth.Incidence of composite outcome NEC stage II or III, LOS or death, and its separate components [18]Incidence of moderate and severe BPD, including postnatal steroid prescription for BPD and total ventilation days [19, 20]Incidence of intraventricular hemorrhage (IVH) including posthemorrhagic ventricular dilatation (PHVD) and/or periventricular leukomalacia (PVL) [21]Incidence of retinopathy of prematurity (ROP) [22]

Neurodevelopmental outcome will be assessed in the included infants qualifying for regular long-term follow-up program at 2, 5.5, and 8 years corrected age, i.e. all infants with GA < 30 weeks, birth weight < 1000 g, or birth weight < 1500 g classified as small for GA. Neurodevelopmental impairment is defined as follows: a cognitive and/or motor composite score less than 85 on the BSID-IV-NL; cerebral palsy greater than level II on the Gross Motor Function Classification System; hearing or visual impairment [23]. Lastly, an economic evaluation will be performed alongside the clinical study to estimate cost-effectiveness (defined as costs per unnecessary antibiotic prescription). The costs and benefits of an added presepsin-guided decision to the Dutch EOS guideline will be compared with care as usual (e.g. including medical costs of hospital days, antibiotic use, laboratory tests and labour costs).

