**Methods:**

The PRESAFE trial is a multicentre, randomized controlled trial (RCT), including a concurrent observational study. Presepsin levels are determined from umbilical cord blood or during the first regular blood draw in all infants born < 32 weeks gestation. Infants who qualify for empirical antibiotics according to the Dutch EOS guideline are categorized as moderate or high risk for EOS based on prespecified high-risk criteria. Infants not qualifying for empirical antibiotics are categorized as low risk. Preterm infants with a moderate risk for EOS are randomized 1:1 into an intervention arm and a comparator arm. In infants allocated to the intervention arm, empirical antibiotics will only be started above a prespecified presepsin level of ≥ 645 pg/ml. In the comparator arm, infants will be treated according to the standard of care following the Dutch EOS guideline, equivalent to starting empirical antibiotics. The co-primary outcomes of the RCT are the incidence of culture-proven EOS (non-inferiority) and unnecessary antibiotics administration (superiority). The required sample size for the RCT is 900 patients. Infants with a high- or low-risk of EOS are excluded from randomization but included in a concurrent observational study and treated according to the Dutch EOS guideline. The primary outcome of this part is the diagnostic accuracy of presepsin.

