### Intervention description {11a}

Infants at moderate risk of EOS will be randomly assigned (1:1 ratio) to the intervention or comparator arm. In the intervention arm, empirical antibiotics will only be started when the presepsin level is ≥ 645 pg/ml [14]. The result of the presepsin test will be communicated with the attending physicians as positive or negative without mentioning the exact level. Infants allocated to the comparator arm and those who will not be randomized will be treated according to standard care following the Dutch EOS guideline, with the treating physician and research team blinded to the presepsin test result.

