### Criteria for discontinuing or modifying allocated interventions {11b}

In case of clinical deterioration of infants not receiving antibiotics allocated in the RCT intervention arm (based on a presepsin level under the threshold), the treating physician can decide to start antibiotic treatment after performing a sepsis evaluation (blood culture) if the infant fulfills at least one of the high risk criteria (Table 1). A second blood culture does not have to be performed when antibiotic treatment is started within 12 h after birth and thus after the first blood culture.

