## Statistical methods

### Statistical methods for primary and secondary outcomes {20a}

Analyses for both co-primary outcomes will be performed using the intention-to-treat principle and additionally using the per-protocol principle for the co-primary non-inferiority outcome to evaluate consistency of both analysis approaches compliant with recommendations for non-inferiority analyses [25]. The absolute between-RCT-groups difference in the co-primary non-inferiority outcome (incidence of culture-proven EOS) (intervention—control) with its one-sided 95% confidence interval (CI) will be calculated. When the upper limit of this one-sided 95% CI is below 2%, non-inferiority can be claimed. The between-RCT-groups difference in proportions of the co-primary superiority outcome (unnecessary antibiotics administration) will be studied under a common superiority hypothesis and expressed as a 2-sided 95% CI and analyzed using Fisher’s exact test and mixed effects modeling with site as a random effect and GA as fixed factor (2-sided *p* < 0.05 considered statistically significant). Analyses of secondary outcomes will be performed according to the intention-to-treat principle using common two-tailed hypothesis tests with alpha equal to 0.05 and using two-sided 95% CIs. Because the analyses of the secondary outcomes are considered exploratory, no correction for type I error will be made. Differences between groups in continuous variables will be analyzed with Student’s *t*-test or, if continuous data is not normally distributed, the Mann–Whitney *U* test will be used. Categorical variables will be compared with the chi-squared test or Fisher’s exact test, as appropriate. Furthermore, mixed effects modeling will be performed with site as a random effect and including randomization stratification factors as appropriate.

The observational part of the study will focus on diagnostic accuracy analysis of presepsin, such as sensitivity, specificity, positive predictive value, negative predictive value, and receiver operating characteristic curves with optimal cut-off values per subgroup.

A detailed statistical analysis plan comprising all study outcomes will be completed before database lock and published separately.

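### nSOFA severity is compared only among infants treated for more than 3 days, a group that the allocated strategy helps to select, so the comparison is neither randomised nor intention-to-treat

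*Protocol article*

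**What the plan says.** All references are to the Protocol article.

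- **Who is analysed.** Secondary outcomes lists "Sepsis-related severity of illness using the neonatal Sequential Organ Failure Assessment (nSOFA) score in infants treated with antibiotics > 3 days".
- **When they are scored.** The same section says "The nSOFA score will be calculated 3 times a day within the first 3 days of antibiotic treatment" and "Severe illness is defined as a nSOFA score of ≥ 4 within the first 3 days of antibiotic treatment". The clock starts with the antibiotics, so an infant without antibiotics has no scoring window.
- **Who gets antibiotics.** Under Intervention description {11a}, "In the intervention arm, empirical antibiotics will only be started when the presepsin level is ≥ 645 pg/ml". The abstract describes the comparator as "standard of care following the Dutch EOS guideline, equivalent to starting empirical antibiotics".
- **Later starts.** Section {11b} lets the physician start antibiotics in a presepsin-low infant who deteriorates and meets a high-risk criterion.
- **Analysis principle.** Section {20a}: "Analyses of secondary outcomes will be performed according to the intention-to-treat principle". It adds: "Because the analyses of the secondary outcomes are considered exploratory, no correction for type I error will be made".
- **Timeline.** The participant timeline {13} marks sepsis-related severity at 0, 48, 72 and 168 h for RCT infants and does not limit it to treated infants.

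**The concern.** Being treated for more than 3 days is an event after randomisation, and the trial is designed to change the step that leads to it. Nearly every comparator infant starts antibiotics; in the intervention arm only presepsin-positive infants do, apart from later starts. The subset in the intervention arm is therefore a presepsin-enriched selection, while the subset in the comparator arm is not.

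The duration decision may also differ between arms. Intervention physicians are told whether the test is positive or negative, comparator physicians are not, and allocation is open.

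Three kinds of infant fall outside the analysed set: those never treated, those treated for 3 days or less, and those who die before exceeding 3 days of treatment. Presepsin-low infants who start antibiotics later are included only if treated for more than 3 days, and their 3-day window then opens at a later age than that of an infant treated from birth. The infants in whom withholding could matter are thus the least consistently measured on this outcome. An arm difference could appear with no effect on illness, and a real one could be blurred.

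**Working it through.** **1. The plan's own figure.** No sample size or event count is given for nSOFA. The per-arm number used below comes from Sample size {14}: EOS incidence 1.4% in both arms, margin 2%, one-sided 5%, power 80%.

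n = (1.645 + 0.842)² × 2 × 0.014 × 0.986 / 0.02² ≈ 427 per arm, and 427 / 0.95 rounds up to 450. Both stated figures reproduce.

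**2. Size of the two subsets.** Inputs from {14}: sensitivity 100%, specificity 54% (95% CI 41–62%), and about 70% of controls stopping within 72 h, so about 30% continue.

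- Control: 0.30 × 427 = 128.
- Intervention, share starting antibiotics: 0.014 + 0.986 × 0.46 = 0.4676. If prolonged treatment is unrelated to presepsin and EOS: 0.30 × 0.4676 × 427 = 60.
- Alternatively, suppose all EOS infants are treated beyond 3 days. EOS: 0.014 × 427 = 5.98. Non-EOS infants in the control subset: 128.1 − 5.98 = 122.1. Intervention subset: 5.98 + 0.46 × 122.1 = 62 (78 at specificity 41%, 52 at 62%).

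Both routes assume no later antibiotics in presepsin-low infants. Either way, the intervention subset is about half the control subset.

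**3. What this does when the strategy has no effect on illness.** The document gives no severity rates. Assume, for illustration, that severe illness occurs in 50% of EOS infants, 20% of presepsin-high non-EOS infants and 5% of presepsin-low non-EOS infants, the same in both arms. At specificity 54%:

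- Control: 5.98 × 0.50 + 56.18 × 0.20 + 65.95 × 0.05 = 17.5; 17.5 / 128.1 = 13.7%.
- Intervention: 5.98 × 0.50 + 56.18 × 0.20 = 14.2; 14.2 / 62.2 = 22.9%.
- Ratio 1.67, though nothing differs except who is counted. With pooled proportion 31.7 / 190.3 = 0.167, z = 0.092 / √[0.167 × 0.833 × (1/128.1 + 1/62.2)] = 1.60, p about 0.11.

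**4. Sensitivity to the assumptions.** Ranges are over specificity 41–62%. The last column lets 20% of the presepsin-low infants in this subset later receive more than 3 days of antibiotics.

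| Assumed severe risk: EOS / presepsin-high / presepsin-low | Ratio, no later starts | Ratio, 20% later starts |
|---|---|---|
| 50% / 20% / 5% | 1.44–1.87 | 1.31–1.54 |
| 50% / 30% / 10% | 1.36–1.69 | 1.26–1.43 |
| 50% / 10% / 10% | 1.10–1.23 | 1.07–1.14 |

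The last row shows that a spurious ratio remains even with equal risk in all non-EOS infants, because EOS cases form a larger share of the smaller subset. In every row presepsin-low infants are no sicker than presepsin-high ones; if that were reversed, the ratio could fall below 1.

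**The case against.** The strongest reply concerns importance. This is one exploratory secondary outcome. Safety rests on culture-proven EOS as a co-primary outcome, on overall in-hospital mortality as the focus of the interim review, and on expedited reporting of sepsis-related death and of later antibiotic starts in intervention infants. A statistical analysis plan covering all outcomes is promised. All of this stands, and it limits the consequence. It does not remove the point: the restriction is written into the outcome definition, and the exploratory label is given as the reason for omitting a type I error correction, which does not address selection. A later analysis plan can change the denominator, but scores for untreated infants must still be obtained, and recruitment has been running since September 2024.

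Three stronger readings are tempting and are not supported.

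- A reader might infer that nSOFA is the main measure of harm from withholding. The document gives it no such role.
- A reader might infer that early deaths are hidden. They leave this measure, not the trial: sepsis-related mortality and death as a component of the composite are separate outcomes, and mortality is compared by arm at the interim.
- A reader might place 20 severe cases in each subset, obtain 20/128 = 15.6% against 20/60 = 33.3% (z = 2.77, p about 0.006), and expect a significant false signal. That requires every severe case in both arms to fall inside the subset, with none presepsin-low and lost. Its ratio, 2.13, exceeds every ratio in the table.

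It is also too strong to say that infants initially left untreated are never scored: those who start later and are treated for more than 3 days are.

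**Conclusion.** The point holds in structure and needs no assumed rates: the denominator is determined after randomisation by something the intervention changes, the scoring clock is tied to treatment, and this contradicts the intention-to-treat statement. On the protocol's figures the subsets are about 128 against 60 per 427, before later antibiotic starts.

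The size and direction of the bias are not established. With no true effect, the spurious ratio is about 1.1 to 1.9 under the assumed severity rates, with the published specificity applied to the subset treated beyond 3 days. Statistical significance cannot be predicted. The co-primary analyses, the sample size and the mortality stopping rule are untouched. What is compromised is the between-arm reading of sepsis severity.

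**What to change.** Define the between-arm outcome as nSOFA ≥ 4 at any time, in all randomised infants, over one fixed window counted from birth or randomisation and identical in both arms. Count death within the window as severe. The window should be long enough to capture illness after later antibiotic starts; the participant timeline already marks severity up to 168 h, and outcome text and timeline should be made to agree. Keep the subset treated for more than 3 days as a descriptive summary, without a test between arms.

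The cost is changed wording in the outcome definition, analysis plan and case report form, plus nSOFA abstraction for more infants, who are already in hospital. Treatment and sample size do not change. Recruitment is expected to run to late 2027, so an early change leaves fewer infants unscored.

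One shortcut should be avoided: counting, over all randomised infants, those treated for more than 3 days with nSOFA ≥ 4 plus deaths before day 3. It needs no new scores but still conditions on treatment duration. On the no-effect counts above, before deaths, it gives 17.5/427 = 4.1% in control against 14.2/427 = 3.3% in intervention, so withholding would look safer when nothing differs.

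### The only summaries the protocol defines for the nSOFA and BSID-IV-NL scores are cuts; adding a comparison on the score scale would recover information already collected

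*Protocol article*

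**What the plan says.** All references are to the protocol article.

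**Secondary outcomes, nSOFA.** The outcome is sepsis-related severity by the "neonatal Sequential Organ Failure Assessment (nSOFA) score in infants treated with antibiotics > 3 days". On frequency: "The nSOFA score will be calculated 3 times a day within the first 3 days of antibiotic treatment". That is 3 × 3 = 9 readings per infant. The summary is then given twice: "Severe illness is defined as a nSOFA score of ≥ 4 within the first 3 days of antibiotic treatment", and again "A cut-off value of 4 will be used to differentiate between severe illness and non-severe illness". No other summary, such as a maximum, mean or trajectory, is defined.

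**Secondary outcomes, neurodevelopment.** Impairment is a composite. One component is "a cognitive and/or motor composite score less than 85 on the BSID-IV-NL"; the others are "cerebral palsy greater than level II on the Gross Motor Function Classification System; hearing or visual impairment". The scores have no other stated use.

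**Statistical methods for primary and secondary outcomes {20a}.** "Analyses of secondary outcomes will be performed according to the intention-to-treat principle using common two-tailed hypothesis tests with alpha equal to 0.05". Continuous variables go to a t-test or Mann–Whitney test, and mixed models with site as a random effect are added. For the rest: "Categorical variables will be compared with the chi-squared test or Fisher’s exact test, as appropriate". None of these methods is assigned to nSOFA or BSID by name. The secondary analyses are called exploratory, and a separate analysis plan covering all outcomes is announced.

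In the same list, total antibiotic days and total ventilation days are kept as counts.

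**The concern.** A graded score cut at one point treats all infants on the same side as equal. An infant whose highest nSOFA is 4 counts the same as one with a much higher score, and a BSID score of 86 counts the same as 110. If the arms are compared only on the cut, a general shift that moves few infants across it is hard to see.

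This matters because nSOFA and BSID are the main graded measures of sepsis severity and later development in a trial about withholding antibiotics. They are also available in fewer infants than the 427 per arm of the sample size: nSOFA only in those treated for more than 3 days, neurodevelopment only in those who qualify for regular follow-up. A modest worsening could be reported as no difference and read as reassurance. All the scores needed to avoid this are already collected.

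**Working it through.** **1. The plan's own figures.** None is stated for nSOFA, BSID or impairment: no event rate, SD, effect or power. The co-primary sample size does reproduce: (1.645 + 0.842)² × 2 × 0.014 × 0.986 / 0.02² ≈ 427 per arm, and 427 / 0.95 gives 450. Superiority power for 70% v 40% at 427 per arm exceeds 99.9%, so a finer scale would gain nothing there. Everything below rests on assumptions.

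**2. General size of the loss.** For a normal score with a share p beyond the cut c, the efficiency of the cut relative to the full score is φ(c)² / [p(1 − p)].

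| Share beyond cut | Efficiency | Information lost | Power if the full score has 80% |
|---|---|---|---|
| 50% | 0.64 | 36% | 61% |
| 25% | 0.54 | 46% | 54% |
| 16% | 0.44 | 56% | 46% |

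With 10% or 5% beyond the cut, 66% or 78% is lost. If full-score power is only 10–20%, the loss in power is 2–9 points. nSOFA is ordinal and taken here to pile up at zero, so this is a guide only and step 3 simulates it.

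**3. nSOFA.** Group sizes from Sample size {14}: about 70% of control infants stop within 72 h, so 0.30 × 427 = 128 continue. With specificity 54%, about 46% of uninfected infants test positive: 0.46 × 128 = 59, or about 60 once all EOS cases are kept. Assumed: a 10-level score, 30% of comparator infants at score 0, 10/20/30% at 4 or more, and a proportional-odds shift towards worse scores in the intervention arm. For example, at odds ratio 2 a share of 10% becomes 0.222 / 1.222 = 18.2%. Tests are Wilcoxon on the score and a two-proportion test on the cut, two-sided 5%. With no effect they reject in 4.9% and 4.7%.

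| Infants | Odds ratio | Power, full score | Power, cut (10/20/30% at ≥ 4) |
|---|---|---|---|
| 128 v 60 | 1.5 | 30% | 15 / 21 / 25% |
| 128 v 60 | 2 | 70–71% | 35 / 51 / 58% |
| 427 v 427 (if all were scored) | 1.5 | 92–93% | 48 / 71 / 83% |

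For the subset as defined, the difference is 15/9/5 points at odds ratio 1.5 and 36/20/13 at odds ratio 2. With 50% at score 0 it is about 5–34 points. With 427 per arm and odds ratio 2 or more, both analyses are near 100% and little or nothing is gained.

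**4. BSID.** Assumed: SD 15, cognitive–motor correlation 0.6, comparator mean 95–100, 200 assessed per arm.

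| Shift | Mean of the two scores | Cognitive score alone | Either score < 85 |
|---|---|---|---|
| 3 points | 59–62% | 51% | 37–38% |
| 4 points | 84–85% | 75–77% | 59–62% |

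The middle column checks by hand: SE = 15 × √(2/200) = 1.5, so a 3-point shift is 2 SE and power is Φ(2 − 1.96) ≈ 0.52. With 150–300 per arm and shifts of 2–5 points, the mean score gains about 7–29 points. The simulated cut leaves out cerebral palsy, hearing and vision, so it approximates the impairment composite and is not the composite itself.

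**5. Dependence on inputs.** Other reasonable choices of score shape, subset size and effect give losses from about 2 to over 50 points. The 5–35 range describes the scenarios for the nSOFA subset and BSID above. It is not a bound.

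**The case against.** **The analysis plan may already do this.** The article condenses a fuller protocol and defers detail to a plan that is not shown. This stands in part: the article does not forbid a comparison of scores, and its list of methods leaves room for one. A reader might infer that each score will certainly be reduced to yes/no before the arms are compared. The text does not say that. What it does contain is a threshold stated twice as the nSOFA definition, next to outcomes left as counts. That is a stated choice, and an analysis plan would carry it forward by default.

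**The BSID cut is one part of a composite.** This stands. The composite has no single continuous scale, so a score comparison can only sit beside it.

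**The power figures are not the trial's.** This stands. A shift along the whole scale favours the full-score test, and an effect confined to the severe tail would show little or no gain. A reader might also infer that planned power is being lost. No power is claimed for these outcomes.

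**The nSOFA comparison is not randomized.** This stands. Being treated for more than 3 days happens after randomization and depends on the intervention, since infants with a negative presepsin result are not started on antibiotics. More power in that subset can also make a selection difference look significant. Infants never treated that long are not scored at all. A reader might infer that a finer scale makes this a sound safety comparison; it does not.

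**The cuts are cited clinical definitions.** This stands. Nothing in the document shows either threshold to be wrong, and making them merely descriptive would be a debatable trade. The case is for adding an analysis.

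**Conclusion.** The point holds as a minor recommendation. A cut at 4 is the only nSOFA summary defined, and BSID enters only as below 85 within a multi-domain composite. Relying on these alone wastes collected information, at a cost of roughly 5 to 35 points of power in the scenarios shown. That range rests on an assumed score shape, a proportional-odds shift, subset sizes of about 128 v 60, and for BSID an SD of 15 with 150–300 infants per arm. The gain is small or nil where power is already near 100% or the effect is confined to the severe tail.

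The sample size, stated power and both co-primary conclusions are unaffected. The case is cleaner for BSID, which is not conditioned on length of treatment, than for nSOFA.

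**What to change.** Keep the proportion with nSOFA of 4 or more and the impairment composite exactly as defined. Add to Secondary outcomes, and carry into the analysis plan:

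1. The BSID-IV-NL cognitive and motor composite scores at the 2-year assessment are each compared between arms as continuous outcomes, using the mixed model already described in {20a} (site random, GA fixed).
2. The highest nSOFA score in the scoring window is compared as an ordinal outcome, by a proportional-odds model or the Mann–Whitney test already listed. State beside it that the subset treated for more than 3 days forms after randomization, so the result is to be read with caution on either scale.

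The cost is two sentences and a few lines of code, with no new data. The downsides are a few more exploratory estimates, and that an odds ratio or mean difference is less immediate to clinicians than a percentage. Keeping the cut proportions alongside answers the second.
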